### Data collection and handling

The study coordinators (HS and LV) will collect the data. All data will be handled confidentially and anonymously. A subject identification code is used to link the data to the subject. The study coordinators safeguard the key to the identification code. The handling of personal data will comply with the Dutch Personal Data Protection Act.

To investigate the accuracy of ^18^F-FDG PET-CT and 4-phase liver CT in the diagnosis of LTP after IRE, twelve months after the last IRE treatment blinded data sets from all centers will be reviewed separately and independently by two designated radiologists ([name] and [name]) and two nuclear medicine physicians (OH and EC) in a consensus reading. Each lesion will be scored on a separate form on a one to five scale (Table 3) [25]. The reviewers will be blinded to the results of the other imaging modality and to the final oncologic outcome as determined by the standard of reference.

**Table 3 Tab3:** Study form for reviewers’ results (per lesion)

Study number		Reviewer number
Score	Definition	Explanation
1	Normal	Confident that no tumor recurrence is present in the ablation zone
2	Probably benign	The appearance of the ablated lesion is compatible with post-ablational inflammation or rim-like characteristics
3	Equivocal	There is doubt whether the imaging features indicate local tumor progression or inflammation
4	Probably malignant	Confident about local progression in the ablation zone
5	Impaired quality	Quality of the images precludes adequate diagnosis
Comments:		

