**Methods/design:**

In this single-arm, multicenter phase II clinical trial, twenty-nine patients with ^18^F-FDG PET-avid CRLM ≤ 3,5 cm will be prospectively included to undergo IRE of the respective lesion. All lesions must be unresectable and unsuitable for thermal ablation due to vicinity of vital structures. Technical success is based on ceMRI one day post-IRE. All complications related to the IRE procedure are registered. Follow-up consists of ^18^F-FDG PET-CT and 4-phase liver CT at 3-monthly intervals during the first year of follow-up. Treatment efficacy is defined as the percentage of tumors successfully eradicated 12 months after the initial IRE procedure based on clinical follow-up using both imaging modalities, tumor marker and (if available) histopathology. To determine the accuracy of ^18^F-FDG PET-CT and ceCT, both imaging modalities will be individually scored by two reviewers that are blinded for the final oncologic outcome.

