### Sample size calculation and statistical considerations

Based on the current literature our hypothesis is that 10 % of the treated tumors will recur after the initial treatment (primary technique efficacy 90 %), which implies a local recurrence rate of 0.1 [5, 30]. Choosing a target width of 0.25 with p ≤ 0.05, we used the confidence interval formula “Exact” for two-sided confidence intervals for one proportion (Clopper-Pearson) [31, 32]. With this formula, actual width is 0.249, with a 95 % confidence interval of 0.020–0.269. This calculation results in a sample size of 29 patients. Considering a 5 % loss to follow-up, the total number of patients needed is 31.

All clinicopathological and procedural variables will be described and analyzed. Continuous variables will be summarized with standard descriptive statistics including means, standard deviations, medians and ranges. Categorical variables will be summarized with frequencies. *P*-values ≤ 0.05 will be considered statistically significant. Univariate survival analysis will be performed using the Kaplan-Meier method. Differences in local recurrence rate between subgroups like tumor size and adjuvant chemotherapy will be analyzed descriptively since the expected number of recurrences is too small for statistical analysis.

The accuracy of ^18^F-FDG PET-CT and 4-phase liver CT in diagnosing local recurrences will be investigated by comparison to the reference standard. Interobserver-variability will be determined using Cohen’s Kappa. Sensitivity and specificity of both techniques will be calculated with their respective 95 % confidence intervals. McNemar’s test is used to assess a statistically significant difference between both imaging modalities.

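### The imaging reads are described as both independent and by consensus; if readers go straight to consensus, the planned interobserver kappa cannot be computed

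*Protocol article*

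**What the plan says.** Four places in the protocol article bear on how the scans are read and analysed.

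- **Abstract, Methods/design:** "both imaging modalities will be individually scored by two reviewers that are blinded for the final oncologic outcome".
- **Data collection and handling, reading mode:** the blinded data sets "will be reviewed separately and independently by two designated radiologists" and two nuclear medicine physicians. The end of that sentence and the start of the next read "in a consensus reading. Each lesion will be scored on a separate form on a one to five scale". A later sentence adds: "The reviewers will be blinded to the results of the other imaging modality and to the final oncologic outcome".
- **Data collection and handling, Table 3:** the per-lesion form has a field for the reviewer's number and five codes: 1 normal, 2 probably benign, 3 equivocal, 4 probably malignant, 5 impaired quality. Code 5 is explained as "Quality of the images precludes adequate diagnosis".
- **Sample size calculation and statistical considerations:** "Interobserver-variability will be determined using Cohen"'s kappa, with no weighting mentioned. Sensitivity and specificity of each modality follow, with 95% intervals, and McNemar's test compares the two modalities.

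Primary and secondary objectives lists the accuracy of the two modalities among the secondary endpoints.

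**The concern.** Cohen's kappa needs two ratings of the same scan, made without conferring. A consensus reading produces one. A sentence that asks for both modes leaves the reading team to choose, and one of the choices removes the data for an analysis that the article commits to.

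The loss would be hard to repair. The reading session is held a year after the final procedure. If individual scores are not captured then, the only remedy is to repeat the session, with readers who have already discussed the cases.

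The form raises a smaller question. Codes 1 to 4 rise in suspicion of local tumor progression (LTP), while code 5 says that the scan cannot be judged. Numbering it on the same scale invites an analyst to handle it as a score.

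**Working it through.** **1. What each reading of the text leaves for kappa.** Kappa = (p_o − p_e)/(1 − p_e), where p_o is the observed agreement between two raters and p_e the agreement expected by chance from their margins. Both terms need two ratings per lesion within a modality.

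- *Consensus only.* One score per lesion per modality. There is no second rating, so p_o does not exist and kappa is undefined. If both readers' forms merely copy the agreed score, p_o = 1 and kappa = 1, which says nothing about the readers.
- *The CT pair and the PET pair work independently of each other, with consensus inside each pair.* Still one score per modality. The only agreement left to measure is CT against PET, which is not interobserver variability.
- *Individual scores only.* Two scores per modality. Kappa can be computed, but the consensus wording then has no function, and the article does not say which of the two scores enters the accuracy analysis.
- *Individual scores, then consensus.* Two individual scores and one agreed score. Kappa uses the first two and accuracy uses the third. Every stated analysis has its data, but the article does not state this order.

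Under the first two readings the planned kappa has no usable data.

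**2. Whether the position of code 5 matters.** Take an assumed two-reader table (not trial data) of 29 lesions scored 1 to 4. There are 14, 5, 1 and 3 agreements on codes 1, 2, 3 and 4, which makes 23, and both readers have margins 16, 8, 2, 3. Add two lesions on which one reader gives 5 and the other does not, once in each direction, so n = 31 and p_o = 23/31.

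- Disagreements of 1 against 5: margins 17, 8, 2, 3, 1; p_e = (289 + 64 + 4 + 9 + 1)/961 = 367/961; kappa = (713 − 367)/(961 − 367) = 346/594 = 0.582.
- Disagreements of 4 against 5: margins 16, 8, 2, 4, 1; p_e = 341/961; kappa = (713 − 341)/(961 − 341) = 372/620 = 0.600.

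Placing code 5 first instead of last leaves both values unchanged, because unweighted kappa ignores order. Weighted kappa would change. With quadratic weights it goes from 0.511 to 0.871 in the first case and from 0.906 to 0.471 in the second. The article plans no weighting.

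**3. What shared code 5 scores do to unweighted kappa.** On the same 29 lesions alone, kappa = (23 × 29 − 333)/(841 − 333) = 334/508 = 0.657, where 333 = 256 + 64 + 4 + 9. Add two lesions that both readers call unreadable: kappa = (25 × 31 − 337)/(961 − 337) = 438/624 = 0.702. Agreement on LTP is the same in both tables. The rise comes only from agreement about image quality.

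**4. What code 5 can do to accuracy.** The article's recurrence rate of 0.1 on 29 patients, assuming one lesion each, gives 2.9, so about 3 LTPs and 26 lesions without. Assume one LTP and two other lesions are scored 5, and all the rest are classified correctly.

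- Code 5 counted as positive: sensitivity 3/3, specificity 24/26 (0.923).
- Code 5 excluded: 2/2 and 24/24.
- Code 5 counted as negative: 2/3 (0.667) and 26/26.

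**5. Sample size.** The exact interval at n = 29 and proportion 0.1 is 0.0203 to 0.2691, width 0.2487; at n = 28 the width is 0.2535. So 29 is the smallest n that meets the 0.25 target, and 29/0.95 = 30.5 rounds up to 31. The stated figures reproduce and do not depend on the reading procedure.

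**The case against.** The strongest reply is that the article gives enough to infer a workable procedure. The abstract has individual scoring, and the Table 3 form identifies the reviewer. Both fit individual reads followed by consensus, with kappa taken from the former. This stands as far as it goes: a reader might infer that the kappa and accuracy results are invalid as planned, and the documents do not support that. What they show is an unstated order, and one literal way of following it loses the individual scores.

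A reader might also infer from Table 3 that unreadable scans are ranked as more suspicious than malignant ones. The table's own explanation makes code 5 a non-diagnostic category, and no weighted kappa, ROC analysis or high-score cut-off is planned. For the plain kappa that is named, its position has no effect (step 2). What survives is narrower: shared code 5 scores would count as agreement, and nothing on the form itself keeps the code out of the accuracy analysis.

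Finally, the rule for which scores count as positive may sit in the full protocol or analysis plan, neither of which is shown, so its absence here is not a fault.

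**Conclusion.** The point holds as a conflict over reading mode. The sentence under Data collection and handling contradicts itself and does not fit the abstract or the planned kappa. The consequence is conditional: if readers go directly to consensus, kappa within each modality cannot be computed; if they score alone first, it can. The documents do not settle which will happen.

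The code 5 point is secondary. The shift from 0.657 to 0.702 and the three accuracy results rest on assumed tables and show direction only. It is tempting to add that a single reclassified LTP moves sensitivity by 33 points (1/3). That follows from about three expected events under any reading scheme, so it does not measure this defect.

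Only the imaging-accuracy secondary endpoint and its observer agreement are affected. The change should be made before the reading session, because unrecorded individual scores cannot be recovered afterwards.

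**What to change.** Replace the sentence on reading mode with a stated sequence, and align the abstract and the statistical section with it:

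1. Each reader scores every lesion alone, blinded as already planned, and locks the form before any discussion.
2. Kappa is computed within each modality pair (the two radiologists for CT, the two nuclear medicine physicians for PET-CT) from the locked scores.
3. Each pair then agrees a consensus score, still blinded to the other modality and to the outcome. This score feeds sensitivity, specificity and McNemar's test.
4. Image quality is recorded as a separate yes/no flag, leaving 1 to 4 as the suspicion scale. Non-diagnostic scans are counted and reported for each modality. They do not enter kappa as agreement on LTP and do not enter the accuracy analysis as positive.

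The cost is a revised form, a few sentences of text and a little extra time to lock individual scores. The readers, patients and scans stay the same.

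### Image-reading score 4 is defined as probable but explained as confident, so a likely but uncertain local progression can be scored 3 or 4

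*Protocol article*

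**What the plan says.** The article's Data collection and handling section sets up a blinded reading twelve months after the last IRE treatment, by two radiologists and two nuclear medicine physicians. On the form, "Each lesion will be scored on a separate form on a one to five scale". Table 3 has a Definition column and an Explanation column:

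- Score 1, normal: "Confident that no tumor recurrence is present in the ablation zone".
- Score 2, probably benign: "The appearance of the ablated lesion is compatible with post-ablational inflammation or rim-like characteristics".
- Score 3, equivocal: "There is doubt whether the imaging features indicate local tumor progression or inflammation".
- Score 4, "Probably malignant": "Confident about local progression in the ablation zone".
- Score 5, impaired quality: "Quality of the images precludes adequate diagnosis".

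The section on sample size and statistical considerations says how the readings are used: "Sensitivity and specificity of both techniques will be calculated with their respective 95" % confidence intervals, McNemar's test to compare the two modalities, and Cohen's kappa for interobserver variability. Accuracy of PET-CT and CT in detecting LTP is listed among the secondary endpoints.

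**The concern.** The form exists to grade certainty, and in the row for score 4 its two columns name different degrees of it. The word used to explain 4 is the word used to explain 1, the most certain benign grade. No malignant grade lies above 4, because 5 records image quality. A reader who leans towards progression without being confident is therefore pointed to 4 by the Definition. The Explanation of 4 excludes that reader, and the Explanation of 3 can also be read to fit. Two careful readers could score the same scan differently and both be following the form.

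The trial expects this state of mind. Its Discussion says that inflammation after IRE can persist for months and makes PET hard to judge, and that reactive tissue and viable tumor can look alike on CT.

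At stake is avoidable misclassification in the imaging-accuracy comparison. On the natural reading, radiologists score CT and nuclear medicine physicians score PET-CT. If the two groups settled the conflict differently, part of any difference between modalities could come from the form. That they would do so is a possibility, not something the article shows.

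**Working it through.** **1. The plan's own figure.** Inputs from the sample size section: recurrence rate 0.10, two-sided 95 % Clopper-Pearson interval, target width 0.25, 5 % loss. With x = 0.1n, the limits are the beta quantiles B(0.025; x, n − x + 1) and B(0.975; x + 1, n − x).

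- n = 28: width 0.2535.
- n = 29: 0.0203 to 0.2691, width 0.2487.
- Allowing for loss: 29 / 0.95 = 30.5, rounded up to 31.

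The stated 29 and 31 reproduce. They serve here only to give the expected number of events.

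**2. The wording, row by row.** Take a reader who judges LTP likely but is not confident.

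| Score | Fits the Definition? | Fits the Explanation? |
|---|---|---|
| 3 | Arguable: leans one way, so not fully equivocal | Yes, if any doubt counts |
| 4 | Yes | No |

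Neither row fits cleanly, so the choice depends on which column the reader follows.

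**3. Expected events.** Assuming one lesion per patient: 0.10 × 29 = 2.9 and 0.10 × 31 = 3.1, so about 3 LTPs.

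**4. One true LTP scored 3 instead of 4.** Sensitivity = detected LTPs / all LTPs.

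- *Assumption A, only score 4 is positive.* With 3 LTPs, sensitivity falls from 3/3 = 1.00 (exact 95 % CI 0.29 to 1.00) to 2/3 = 0.67 (0.09 to 0.99), a shift of 1/3, or 33 points. The shift is 1/m for m LTPs: 50 points for m = 2, 20 for m = 5, 12.5 for m = 8.
- *Assumption B, scores 3 and 4 are both positive.* The lesion is positive either way, so the shift is 0.

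**5. One lesion without LTP scored 4 instead of 3.** With 29 − 3 = 26 such lesions, specificity under A goes from 26/26 = 1.00 (0.87 to 1.00) to 25/26 = 0.96 (0.80 to 1.00 after rounding), about 4 points. Under B the lesion is a false positive either way, so the shift is 0.

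**6. McNemar's test and kappa.** Under A, a changed call in one modality can turn a concordant pair into a discordant one, or the reverse. Under B a move between 3 and 4 changes no pair. Kappa on raw scores can be affected under either assumption, because two readers who enter 3 and 4 for the same scan disagree.

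**The case against.** The strongest reply has five parts.

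- **A matching score exists.** A reader might infer that probable progression has no score at all. The table does not support that: the column headed Definition names probable malignancy at score 4, and on an ordered scale a reader favouring progression has a fair case for choosing it. This stands; the row is ambiguous, not empty.
- **The cut-off is not stated.** A reader might also infer that the line between 3 and 4 is where sensitivity is decided. The article does not say which scores count as positive, and if 3 counts, the deciding line is between 2 and 3. This stands, and the effect is conditional. The cut-off may well be fixed in a full protocol or analysis plan that is not shown, so its absence is not a fault.
- **The 33 points are not specific to this wording.** Any single changed call, for any reason, moves sensitivity by 1/3 when there are three events. This also stands. Nor should the shift be set against the 9-point gap in sensitivity cited in the Discussion (92 % against 83 %), which is background and not a design input. Three LTPs could not resolve such a gap anyway: if all three were discordant in the same direction, the exact two-sided McNemar p-value on them would be 2 × 0.5³ = 0.25.
- **The benign side is not a clean mirror.** Score 2 is explained by appearance and not by a lower level of confidence, so the contrast between the two sides is partial. This stands, but the conflict within row 4 does not depend on it.
- **There are safeguards.** The Imaging section gives LTP criteria for each modality (growth above 20 %, or focal uptake, within 1 cm), and the reading is by consensus. These narrow the room for disagreement. They do not tell a reader which column of row 4 to follow.

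**Conclusion.** The point holds as a wording conflict in the reading form. The Definition and Explanation of score 4 state different certainty, and a reader who finds LTP likely without being confident can defensibly enter 3 or 4.

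Its numerical effect is conditional. With only score 4 positive, one lesion per patient and about 3 LTPs, one such lesion moves sensitivity by about 33 points (12.5 to 50 points for 8 down to 2 LTPs) and can also alter specificity and McNemar's test. With 3 and 4 both positive, those quantities do not change, and only kappa on raw scores could. Patients with several metastases may be included, so the count of target lesions, and with it the expected number of LTPs, could exceed this illustration.

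A reader might infer that the trial's efficacy result is at risk. It is not: the primary efficacy rate follows RECIST and PERCIST against the reference standard, not Table 3. The matter is minor, confined to a secondary endpoint, and worth correcting because the correction is so cheap.

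**What to change.** Before the end-of-trial reading, reword the Explanation of score 4 to agree with its Definition, for example: imaging features favour local tumor progression over inflammation, whether probable or confident. Score 3 is then kept for true equivocation. Give both reader groups the same wording, and check that it agrees with whatever positivity rule the analysis uses.

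A separate definitely-malignant grade is optional. It would be counted as positive together with score 4, so it adds nothing to sensitivity, specificity or McNemar's test, and it would enlarge a form described as running from one to five.

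The cost is one line of text and no extra scans or reads. The downside is a small departure from the present form, whose wording may come from the scale the article cites (reference 25); that cannot be checked here. If so, the change should be noted when the results are reported.

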### Primary and secondary objectives

The primary endpoint of the COLDFIRE-2 trial is efficacy of IRE for CRLM. Secondary endpoints are progression-free survival (PFS) and overall survival (OS). Other secondary endpoints are safety, technical success, and the accuracy of ^18^F-FDG PET-CT and 4-phase liver CT in the detection of LTP after IRE.

Primary efficacy rate is defined as the percentage of target tumors successfully eradicated 12 months after the initial IRE procedure, according to the RECIST and PERCIST criteria. Secondary efficacy rate is defined as the percentage of tumors successfully eradicated 12 months after the initial IRE procedure, including tumors that have undergone successful repeat ablation following identification of LTP [26].

Progression-free survival is defined as the time from the first IRE procedure to the time of radiologic disease progression or death of disease. Overall survival is defined as the time from the IRE procedure until death of disease [27]. Both PFS and OS will be determined using the Metabolic Imaging And Marker Integration (MIAMI) criteria as proposed by Hosein and colleagues, which integrates anatomic response parameters (4-phase liver CT) with two functional parameters: PET activity and CEA levels [28]. For safety analysis, all major adverse events and all adverse events occurring during or within 12 months after IRE treatment will be recorded according to the Common Terminology Criteria of Adverse Events (CTCAE) v4.0 [29]. Pain assessment using the visual analogue scale (VAS) and patient analgesic consumption will be recorded. Patency of vessels and bile ducts on follow-up cross-sectional imaging will be analyzed to identify late complications. Technical success is defined as (1) the ability to successfully deliver all planned pulses according to protocol and (2) complete lesion coverage on post-procedure ceCT or IOUS, and 24–48 h post-procedure MRI [26].

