Irreversible electroporation (IRE) is a novel ablation modality that may overcome some of the limitations of current thermal ablation therapies. It is based on a pulsating current created between multiple needle electrodes placed around the target lesion which alters the existing cellular transmembrane potential. If the duration of the applied electrical pulses is below the charging time of the outer cell membrane, an interaction of the electric field with subcellular structures occurs [9]. This interaction results in permanent permeabilization of the cell membrane, which disrupts cellular homeostasis and ultimately leads to cell death. The irreversibly damaged cells are removed by the immune system [10]. Two main factors stimulate research into IRE as an ablation modality. Since the mechanism of cell death is predominantly nonthermal, connective tissue structure is preserved, so there is no damage to associated blood vessels and bile ducts [11–13]. For the same reason, treatment efficacy is not impeded by heat-sink [14]. This allows for treatment of liver tumors deemed unresectable or ineligible for other focal ablation techniques due to localization near these structures [15].

The capability of IRE to destroy CRLM in humans was recently demonstrated in the COLDFIRE-1 ablate-and-resect trial [16]. In this trial resectable CRLM were treated with IRE, followed by resection one hour later. The investigators demonstrated cell death of the ablated tumors within one hour after IRE, with intact larger vascular and ductal structures within the ablation zone. The first studies investigating hepatic IRE on clinical indication also yield promising results. A systematic review found an overall complication rate of 16 % for hepatic IRE, similar to RFA [17]. However, the tumors treated with IRE were all located near thermally sensitive structures, as opposed to the thermally ablated lesions. Complete tumor eradication was achieved in 67–100 %, and this percentage was even higher for tumors < 3 cm [17]. However, since most studies are retrospective with short-term follow-up using heterogeneous study populations and design, the value of the current evidence remains limited. Also, the optimal imaging modality for follow-up after IRE needs to be analyzed.

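### The endpoint labelled overall survival, and the death component of progression-free survival, count only deaths from the disease, so what is called OS is disease-specific survival

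*Protocol article*

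**What the plan says.** All the definitions are in the protocol article, section Primary and secondary objectives, where PFS and OS are named as secondary endpoints.

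- OS: "Overall survival is defined as the time from the IRE procedure until death of disease".
- PFS: "Progression-free survival is defined as the time from the first IRE procedure to the time of radiologic disease progression or death of disease".
- Assessment: "Both PFS and OS will be determined using the Metabolic Imaging And Marker Integration (MIAMI) criteria". The article describes these criteria as combining CT response with PET activity and CEA.
- Safety, in the same section: "all adverse events occurring during or within 12 months after IRE treatment will be recorded", graded by CTCAE.

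The section Sample size calculation and statistical considerations gives one sentence on survival analysis: "Univariate survival analysis will be performed using the Kaplan-Meier method". It names no competing-risk method. Nowhere does the article widen either event to death from any cause, or say how a death from the procedure or from another cause enters the OS or PFS analysis.

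**The concern.** Overall survival is normally read as time to death from any cause. Here a patient who dies of a procedural complication, of concomitant surgery or of an unrelated illness has no OS event. If that patient has not yet progressed, there is no PFS event either. In a Kaplan-Meier analysis the patient would be censored at death and treated as someone who could still die of the cancer later. Compared with all-cause survival, the estimate can then only stay the same or rise.

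Non-disease deaths are plausible here. Treatment is given under general anesthesia, in some patients at laparotomy with resection or thermal ablation of other lesions. The targets lie next to vessels and bile ducts, and ASA class up to 3 is allowed. The Background reports complications but no mortality: "A systematic review found an overall complication rate of 16 % for hepatic IRE, similar to RFA".

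The trial has a single arm, so readers will set its survival figures beside outside series, as the Background does for resection and thermal ablation. A figure called OS that leaves out treatment-related deaths would favour IRE in that comparison. The definition also requires a judgement on cause of death in an open trial, which an all-cause definition does not need.

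**Working it through.** **1. The plan's own figure.** The article states no figure for OS or PFS; its only calculation is the sample size. Inputs from the sample size section: recurrence proportion 0.10, two-sided 95% Clopper-Pearson interval, target width 0.25, loss to follow-up 5%. The limits are the beta quantiles

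- lower = Beta(0.025; x, n − x + 1)
- upper = Beta(0.975; x + 1, n − x), with x = 0.1n.

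Results:

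- n = 28: width 0.2535, too wide.
- n = 29: limits 0.0203 and 0.2691, width 0.2487, so 29 is the smallest sufficient n.
- Allowance for loss: 29 / (1 − 0.05) = 30.5, rounded up to 31.

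This reproduces the stated 0.020 to 0.269, width 0.249, 29 and 31. Neither OS nor PFS enters, so changing their definitions leaves the sample size as it is.

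**2. Formula for the gap.** Let N be the number of patients, k the non-disease deaths and d the disease deaths by 12 months, with no other censoring.

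- All-cause survival: (N − k − d) / N.
- Disease deaths only, all k non-disease deaths before any disease death: (N − k − d) / (N − k). The gap is (k/N) × (1 − d/(N − k)).
- Disease deaths only, all k non-disease deaths after the last disease death: (N − d) / N. The gap is k/N.

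Other orderings fall between these two. The upper end, k/N, applies when there are no disease deaths or when the non-disease deaths come last. The gap is never negative, and with k = 0 it is zero.

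**3. Numbers.** The article gives no death rates, so k = 1 to 3 and d = 0 to 6 are assumptions.

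| N | k | Lower end (d = 6, non-disease deaths first) | Upper end (k/N) |
|---|---|---|---|
| 31 | 1 | (1/31)(1 − 6/30) = 2.6 points | 3.2 points |
| 31 | 2 | (2/31)(1 − 6/29) = 5.1 points | 6.5 points |
| 31 | 3 | (3/31)(1 − 6/28) = 7.6 points | 9.7 points |
| 29 | 1 | (1/29)(1 − 6/28) = 2.7 points | 3.4 points |
| 29 | 2 | (2/29)(1 − 6/27) = 5.4 points | 6.9 points |
| 29 | 3 | (3/29)(1 − 6/26) = 8.0 points | 10.3 points |

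Example with N = 29, two periprocedural deaths and three later disease deaths: all-cause survival is 24/29 = 82.8%, and the written definition gives 24/27 = 88.9%, a gap of 6.1 points. With N = 31, one procedural death and no disease death, all-cause survival is 30/31 = 96.8%, and the written definition gives 100%.

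**4. PFS.** The same formula applies if d counts progressions and disease deaths, and k counts only non-disease deaths that precede progression. More progressions shrink the lower end. With N = 31, k = 1 at the start and, for illustration, 15 later PFS events, the gap is (1/31)(1 − 15/30) = 1.6 points.

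**The case against.** The strongest case on the other side is about weight. OS and PFS are secondary. The primary endpoint is a per-tumor eradication rate at 12 months, and no sample size or decision rule depends on survival. That stands.

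The censoring of non-disease deaths is also inferred from the event definition and the Kaplan-Meier sentence; the article does not state it. A statistical analysis plan that is not shown could say how those deaths are handled. This stands for the handling. It does not rescue the event itself, which the article fixes as death from the disease while calling the endpoint overall survival.

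A reader might infer more than the text supports:

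- *That a fatal complication would go unseen.* It would not. Adverse events up to 12 months are recorded under CTCAE, so it would appear in the safety data. The fault is that nothing links it to OS or PFS. Nor would the later curve be strictly unchanged, since censoring shrinks the risk set and later disease deaths then weigh slightly more.
- *That both curves are bound to read too high.* They do so only if a non-disease death occurs and, for PFS, only if it precedes progression.
- *That the effect depends on informative censoring.* The gap from all-cause survival follows from the event definition alone and exists even if other-cause deaths are unrelated to cancer risk.
- *That OS and PFS have different time origins because only PFS mentions the first procedure.* In adjacent sentences the natural reading is one index procedure. At most the wording is loose.
- *That calling progression radiologic while using a criterion that includes CEA, or naming MIAMI for OS, distorts the results.* No effect is shown. Imaging and marker criteria cannot date a death, so for OS the MIAMI sentence is awkward but without numerical consequence.

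**Conclusion.** The definitions are wrong for their labels. OS as written is disease-specific survival, and PFS omits deaths from other causes that occur before progression.

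Under the assumptions of 31 patients, 0 to 6 disease deaths by 12 months, no other censoring, and non-disease deaths censored, the 12-month survival estimate rises by about 2.6 to 3.2 points for one non-disease death and about 5.1 to 6.5 points for two. The values 3.2 and 6.5 are upper limits, not a fixed amount per death. The article supplies no rate from which to say how many such deaths to expect.

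This should be fixed, but it is not critical to the trial: the primary efficacy rate and the sample size are unaffected, and safety reporting would still capture a fatal complication. What is at stake is whether the reported OS and PFS can be read alongside series that use the usual definitions.

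**What to change.** 1. Define OS as time from the first IRE procedure to death from any cause.
2. Define PFS as time from the first IRE procedure to progression or death from any cause.
3. Apply the MIAMI criteria to progression only, and take OS out of that sentence.
4. If death from the disease remains of interest, keep it as a separately named disease-specific endpoint, with other deaths as competing events and a stated rule for attributing cause.

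Make the change before analysis, so that known causes of death cannot influence the choice. It changes wording and needs no more patients. The date of death is needed for every patient who dies, and the cause as well if the disease-specific endpoint is kept. The article does not list its data items, so it should be confirmed that these are collected. The downside is that the survival figures may become slightly less favourable.
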